Visit window		−3∼0	Day 30 of treatment	Day 60 of treatment	Day 90 of treatment
Basic history taking					
Informed-consent signature		×	​	​	​
Demographics		×	​	​	​
General data form		×	​	​	​
Medical and prior-treatment history		×	​	​	​
Inclusion/exclusion check		×	​	​	​
Randomisation and enrolment		×	​	​	​
Screening variables					
Bone-mineral density (BMD)		×	​	​	​
Treatment administration					
Test group		​	×	×	×
Control group		​	×	×	×
Efficacy end-points (assessment visits)					
BMD measurement		×	​	​	×
TCM syndrome score		×	×	×	×
Pain score (VAS)		×	×	×	×
Bone-turnover markers (β-CTX, PINP)		×	×	×	×
Inflammatory cytokines (TNF-α, IL-1)		×	×	×	×
Blood-stasis syndrome score		×	×	×	×
Blood-cell indices		×	×	×	×
Safety observations					
Height		×	​	​	×
Blood pressure		×	​	​	×
Electrocardiogram		×	​	​	×
Haematology		×	​	​	×
Liver function		×	×	×	×
Renal function		×	×	×	×
Coagulation profile		×	​	​	×
Adverse-event log		​	×	×	×
Other items					
Concomitant medication / therapy		×			
Study closeout	Withdrawals and drop-outs	×			
	Compliance and safety evaluation form	×			
	Abnormalfindings record	×			
	Studycompletion status	×			
Review & sign-off		×			

Rumo zhentong Yin—composed of Ruxiang (frankincense), Moyao (myrrh), Xuejie (dragon’s blood), Jiangxiang (dalbergia wood), Sumu (sappan wood), Gansong (nardostachys), Xixin (asarum), and Tubiechong (ground beetle)—is an empirical formula created by national TCM master [name] for blood-stasis pain. Although preclinical studies support the anti-inflammatory, analgesic, and bone-protective effects of its ingredients, robust clinical evidence is still lacking (Shima et al., 2016; Lisowska et al., 2018).

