### Withdrawal/discontinuation criteria

Participants will be withdrawn or discontinued if ANY of the following occur: violation of inclusion criteria or fulfillment of any exclusion criterion during the study. Receipt of study treatment for fewer than 30 consecutive days or evidence of poor compliance. Occurrence of serious side-effects, adverse reactions, or allergic reactions. Initiation or modification of concomitant therapies that could influence outcomes without prior approval from the investigator. Withdrawal of informed consent by the participant or their legally authorized representative. Significant disease progression or the development of a new medical condition requiring urgent or alternative.

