#### Concomitant-therapy rules

Throughout the trial, participants are prohibited from using any concomitant medication or intervention that could interfere with the assessment of efficacy or safety. If a participant has a chronic comorbidity requiring ongoing treatment, all concurrent therapies must be documented in the Case Report Form (CRF).

Throughout the trial, participants are forbidden to use any concomitant medication or intervention that could interfere with the assessment of efficacy or safety. If a participant suffers from a chronic co-morbidity that requires continuous treatment, all concurrent therapies must be documented in the Case Report Form (CRF).

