### Outcomes

Primary endpoints: Pain score: Visual Analogue Scale (VAS); Mechanism indicators: 1.Bone-mineral density (BMD); 2.Bone-turnover markers: β-CTX and PINP; 3.Inflammatory cytokines: TNF-α and IL-1.

Secondary endpoints:1.Blood-stasis syndrome score; 2.Hematological indices: serum MCV, RDW-CV, MPV and PDW.

Safety endpoints:Height, blood pressure, 12-lead ECG, routine hematology, liver and renal function tests, and coagulation profile.

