### Randomisation and blinding

Simple randomisation was used. The allocation sequence was generated using SPSS version 24.0. Each unique allocation code was placed in a sequentially numbered, opaque, sealed envelope (numbered 1–114) and stored by an independent custodian. After obtaining informed consent, the next envelope in sequence was opened, and the participant was assigned to either the control or treatment group (n = 57 per group). Because the two interventions could not be blinded to participants, only the outcome assessors, data managers, and statisticians were masked to group assignment. In the Case Report Form (CRF), group labels were replaced with the identifiers“A” and “B.” The master randomisation list (containing the sealed code linking A/B to actual groups) was generated by an external statistician using SAS software and is securely stored by the study administrator. It will remain concealed until after final database lock.

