### Sample size

This is a parallel, two-arm, superiority RCT. A pilot study (Tong-bi Bushen formula for osteoporosis with kidney-deficiency/blood-stasis pattern) showed mean ± SD VAS improvements of 2.45 ± 0.53 (combination) vs. 2.07 ± 0.53 (Western medicine alone). Using an independent-samples t-test in PASS 15.0.1 (α = 0.05 two-sided, power = 0.95, 1:1 ratio) gave 51 participants per arm; allowing 10% attrition, 114 participants (57 per arm) will be enrolled. Data collection and registration All data will be captured in a paper/e-CRF. Investigators will be trained in patient communication, CRF completion and all rating scales. After consent, baseline demographics, BMD, TCM syndrome score, VAS, bone-turnover markers (β-CTX, PINP), inflammatory cytokines (TNF-α, IL-1), blood-stasis score and haematological indices (MCV, RDW-CV, MPV, PDW) will be collected. Follow-up visits occur every 4 weeks for 3 months. Original data and biological samples will be retained for a minimum of 5 years following the conclusion of the study.

An independent Data Monitoring Committee (DMC) consisting of external clinical epidemiologists, data managers and biostatisticians with no conflicts of interest will review safety, CRF accuracy and participant confidentiality every 6 months and will advise on protocol modification or early termination if warranted.

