### Statistical analysis

Statistical analyses will be performed with SPSS 24.0. Continuous variables will be presented as mean ±standard deviation (SD) if normally distributed, or as median (P25, P75) otherwise. Categorical variables will be summarised as frequencies and percentages (*n* [%]). Between-group comparisons of continuous endpoints be conducted using independent-samples t-test (normal) or Mann–Whitney U test (non-normal). Within-group changes over multiple visits will be analysed with repeated-measures ANOVA (normal) or generalised estimating equations (non-normal). If an interaction is significant, simple-effects analysis will follow. Unordered categorical variables will be compared with χ^2^ or Fisher’s exact test. Ordered categorical variables with the rank-sum test. All tests will be two-tailed, with a significance level set at P < 0.05. Missing values will be imputed by last-observation-carried-forward (LOCF) method.

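### Whether a patient who adds pain relief keeps contributing VAS data can turn on approval by an investigator not listed as masked; close that route and keep measuring VAS

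*Protocol article*

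**What the plan says.** All references are to the protocol article.

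- **Concomitant-therapy rules:** "participants are prohibited from using any concomitant medication or intervention that could interfere with the assessment of efficacy or safety". No approval route is given. Ongoing treatment of a chronic comorbidity must be documented in the case report form.
- **Withdrawal/discontinuation criteria:** one trigger is "Initiation or modification of concomitant therapies that could influence outcomes without prior approval from the investigator". Another is "Significant disease progression or the development of a new medical condition requiring urgent or alternative" (the sentence breaks off there). The section does not say whether VAS is still measured afterwards.
- **Drop-out criteria:** non-adherence serious enough to compromise the efficacy evaluation also makes a patient a drop-out.
- **Randomisation and blinding:** participants could not be blinded, and "only the outcome assessors, data managers, and statisticians were masked to group assignment".
- **Outcomes:** "Primary endpoints: Pain score: Visual Analogue Scale (VAS").
- **Statistical analysis:** "Missing values will be imputed by last-observation-carried-forward (LOCF) method". No other missing-data method is named.
- **Table 1:** VAS is scheduled at screening and at days 30, 60 and 90. There is a row for "Concomitant medication / therapy".

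**The concern.** The two rules do not fit together. One bans outcome-influencing therapy outright. The other makes withdrawal depend on whether the investigator agreed beforehand, which leaves room for a patient to use such therapy and stay in.

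The person who decides is not listed as masked, the comparison is add-on without placebo, and the primary endpoint is pain. Added analgesia is foreseeable: patients enter with at least 3 months of pain, the Introduction names NSAIDs as current management, and the basic therapy contains none.

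Added pain relief could then reach the VAS contrast in two ways:

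1. **Approved and retained.** The score includes the relief, and the decision to accept it may differ by arm.
2. **Not approved and withdrawn.** If VAS collection stops, LOCF carries forward an earlier score, usually a less improved one.

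Both routes depend on a post-randomisation decision, and they can push the contrast in opposite directions.

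**Working it through.** **The plan's own figure.** Inputs from the Sample size section: it "showed mean ± SD VAS improvements of 2.45 ± 0.53 (combination) vs. 2.07 ± 0.53 (Western medicine alone"), two-sided α 0.05, power 0.95, 1:1 allocation.

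- Difference: 2.45 − 2.07 = 0.38; SD 0.53.
- Normal approximation: n = 2 × (1.960 + 1.645)² × 0.53² / 0.38² = 50.6, so 51 per arm, as stated.
- Attrition: 51 / 0.9 = 56.7, so 57 per arm and 114 in total, as stated.
- Noncentral t with 51 per arm (100 df) gives power 0.948, the baseline used below.

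The documents give no rate of analgesic use and no withdrawals for it. Everything that follows is an illustration on assumed inputs.

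**Route 1: use accepted, patient retained.** Assume a proportion g of one arm uses the added therapy and none of the other arm does, with r VAS points of relief. The shift is g × r. The SD in the using arm becomes √(0.53² + g(1 − g)r²).

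| r | g | Shift | % of 0.38 | Power, use in controls | Chance of a significant result favouring the decoction, no true effect, use in decoction arm |
|---|---|---|---|---|---|
| 0.5 | 5% | 0.025 | 7% | 0.912 | 0.042 |
| 0.5 | 10% | 0.050 | 13% | 0.863 | 0.067 |
| 1.0 | 5% | 0.050 | 13% | 0.849 | 0.066 |
| 1.0 | 10% | 0.100 | 26% | 0.689 | 0.139 |

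The nominal value for the last column is 0.025. With the SD held at 0.53, power in the two 10% rows is 0.876 and 0.752, so part of the loss is the added variance.

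**Route 2: withdrawn, VAS collection stops, LOCF.** Assume linear improvement over the three visits to 2.07 (control) or 2.45 (combination). LOCF then carries 1/3 of the improvement after day 30 and 2/3 after day 60.

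- Loss per control patient: 2.07 × 2/3 = 1.38 (day 30) or 2.07 × 1/3 = 0.69 (day 60).
- Loss per decoction patient: 2.45 × 2/3 = 1.63 or 2.45 × 1/3 = 0.82.

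| Excess withdrawal | Last VAS day 30 | Last VAS day 60 |
|---|---|---|
| Controls, 5% | +0.069 | +0.035 |
| Controls, 10% | +0.138 | +0.069 |
| Decoction arm, 5% | −0.082 | −0.041 |
| Decoction arm, 10% | −0.163 | −0.082 |

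Against 0.38, excess withdrawal in controls inflates the contrast by 9% to 36%. The same excess in the decoction arm lowers it by 11% to 43%.

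**The case against.** The strongest reply is that the ban already exists and is worded identically for both arms, so the withdrawal clause only states its consequence. On that reading, approval is meant for changes to comorbidity treatment. Neither section names analgesics. This is a fair reading, and it is why the point is a clarification of a rule and not proof of bias. The approval clause as written is still not limited to comorbidity treatment: it covers therapies that could influence outcomes.

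A reader might infer more than the text supports:

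- **That the plan permits pain-relieving co-treatment.** The concomitant-therapy rules imply the opposite. Any permission comes from the approval wording in the withdrawal criteria alone.
- **That withdrawn users will have later VAS filled by LOCF.** This follows only if VAS collection stops at withdrawal, and the article does not say that it does.
- **That a bias of known size is present.** The imbalances are assumed and placed wholly in one arm for Route 1. A 10-point excess withdrawal equals the whole 10% attrition allowance, and 1 point of relief is nearly 2 SD.

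Two further objections stand in part. Route 2 is a weakness of LOCF under unequal drop-out from any cause; this clause is one way into it. Keeping users in follow-up also leaves the effect of unequal analgesic use in the observed contrast.

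Approval criteria and extra sensitivity analyses may well sit in a fuller protocol or analysis plan, and their absence is not held against the article. The mismatch between two stated rules is a different matter.

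**Conclusion.** The point holds as a low-cost improvement that should be made. The two sections disagree on whether outcome-influencing therapy can be accepted, and the written rule lets retention of primary-endpoint data depend on a possibly arm-aware approval. The LOCF consequence is conditional on VAS collection ending at withdrawal.

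Neither direction nor size can be determined from the documents. The calculations show only that, with a planned difference of 0.38 points, an imbalance of a few percentage points between arms would be noticeable. The sample size is unaffected.

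**What to change.** 1. **Withdrawal/discontinuation criteria:** limit investigator approval to changes in chronic comorbidity treatment. The existing ban then covers added pain relief identically in both arms.
2. **Withdrawal/discontinuation and Drop-out criteria:** state that use of a prohibited or added therapy, or stopping study treatment, does not end follow-up unless consent is withdrawn. VAS is still collected at days 30, 60 and 90 and used in the analysis in place of LOCF. Both sections need the change; otherwise the non-adherence clause in the drop-out criteria could still remove the same patients.
3. **Table 1:** record added analgesic use at every visit in the existing concomitant-therapy row, and report it by arm.
4. **Optional:** a sensitivity analysis that adds the same number of VAS points back, for example 0.5 and 1, to scores taken after added analgesia in either arm.

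This removes the discretionary and LOCF routes. It does not remove the effect of unequal analgesic use on observed VAS, which the by-arm report makes visible.

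Cost: a wording amendment, slightly more data entry, and no new visits. Enrolment began on 12 September 2025, so the change needs ethics committee review and a recorded date.

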### Drop-out criteria

Participants are considered drop-outs if ANY of the following occur: Failure to attend scheduled visits on time.

Are lost to follow-up.

Voluntarily withdraw before completing the full course.

Do not adhere to the protocol to an extent that efficacy evaluation is compromised.

### Intervention

Basic therapy: Alendronate sodium (MSD PHARMA [SINGAPORE] PTE.LTD.; Import Drug Registration No. H20160100; 70 mg) 70 mg orally once weekly; Calcium carbonate D_3_ (Wyeth Pharmaceutical Co., Ltd.; National Drug Approval No. H10950029; 600 mg) 600 mg orally daily; Calcitriol soft capsules (Catalent Germany Eberbach GmbH; Import Drug Registration Nos. H20140597 & H20140598; 0.25 µg) 0.5 µg orally once daily; and Elcatonin injection (Shandong Luye Pharmaceutical Co., Ltd.; National Drug Approval No. H20040338; 1 mL:10IU)was administered intramuscularly at 1 mL per dose,twice weekly (all injections were administered by trained hospital nurses). Treatment duration: 3 months. Control group: Conventional intervention only.

Observation group: Conventional intervention plus Rǔ-Mò Analgesic Decoction (10 g Frankincense, 10 g Myrrh, 3 g Dragon’s Blood, 6 g Dalbergia wood, 10 g Sappan wood, 10 g Chinese spikenard, 3 g Asarum root, 6 g Ground beetle).Table 2 summarises the key components of Rumo zhentong Yin.

**TABLE 2 T2:** Key Components of Rumo zhentong Yin.

Chinese name	Latin name/English name	Source organism/Plant part	Quantity (g per day)	Components of Rumo zhentong Yin
Ruxiɑng	Olibanum	Boswellia sacra Flück	10	[figure not shown]
Moyɑo	Myrrha	Commiphora wightii	10	[figure not shown]
Xuejie	Draconis sanguis	Daemonorops draco Bl	3	[figure not shown]
Jiɑngxiɑng	Dalbergiae odoriferae lignum	Dalbergia odorifera T.C.Chen	6	[figure not shown]
Sumu	Sappan lignum	Biancaea sappan	10	[figure not shown]
Gɑnsong	Nardostachyos radix et rhizoma	Nardostachys jatamansi (D.Don) DC.	10	[figure not shown]
Xixin	Asari radix et rhizoma	Asarum sieboldii miq.	3	[figure not shown]
Tubiechong	Eupolyphaga seu polyphaga	Eupolyphaga sinensis	6	[figure not shown]
​	​	土鳖虫不是植物,所以这是他的学名不是 source plant	​	​

All herbal ingredients of Rumo Zhentong Yin were provided by the Pharmacy Department of Xi’an Hospital of Traditional Chinese Medicine and met the quality standards of the Chinese Pharmacopoeia (2020 Edition). Each batch underwent hospital incoming quality inspection. Processing was conducted in accordance with hospital standards; impurities and non-medicinal parts were removed. Specifically, only dried roots and rhizomes of Asarum were used, excluding aerial parts.

Prescriptions were decocted centrally in the hospital decoction room with automatic herbal decoction machines under a unified protocol, including standardized soaking, water addition, boiling time and filtration. The finished decoction was sealed and dispensed to participants. Batch inspection was performed to maintain consistent preparation during the trial.

#### Concomitant-therapy rules

Throughout the trial, participants are prohibited from using any concomitant medication or intervention that could interfere with the assessment of efficacy or safety. If a participant has a chronic comorbidity requiring ongoing treatment, all concurrent therapies must be documented in the Case Report Form (CRF).

Throughout the trial, participants are forbidden to use any concomitant medication or intervention that could interfere with the assessment of efficacy or safety. If a participant suffers from a chronic co-morbidity that requires continuous treatment, all concurrent therapies must be documented in the Case Report Form (CRF).

### Outcomes

Primary endpoints: Pain score: Visual Analogue Scale (VAS); Mechanism indicators: 1.Bone-mineral density (BMD); 2.Bone-turnover markers: β-CTX and PINP; 3.Inflammatory cytokines: TNF-α and IL-1.

Secondary endpoints:1.Blood-stasis syndrome score; 2.Hematological indices: serum MCV, RDW-CV, MPV and PDW.

Safety endpoints:Height, blood pressure, 12-lead ECG, routine hematology, liver and renal function tests, and coagulation profile.

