**Methods:**

A randomized, single-blind, controlled trial was designed to evaluate the efficacy of Rumo zhentong Yin combined with standard therapy for OPP. Eligible OPP patients were recruited and randomly assigned (1:1) to form either the control or treatment group. Both groups received standard treatment. The intervention lasted 3 months, with follow-up evaluations every 4 weeks. Primary outcome was pain scores; secondary outcomes included bone mineral density (BMD), bone-turnover markers, inflammatory cytokines, blood-stasis syndrome score and hematological indices.

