**Trial Registration:**

The trial was registered at the International Traditional Medicine Clinical Trial Registry (www.itmctr.ccebtcm.org.cn) on 2026-01-08 (ITMCTR2026000740).

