### Trial status

Participant recruitment was initially projected to start in January 2025 and close in June 2026, with follow-up assessments expected to finish in December 2026. However, due to preparatory delays, actual enrollment commenced on 12 September 2025, as registered with the International Traditional Medicine Clinical Trial Registry. Recruitment will continue until the registered closing date of 31 December 2026.

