## Limitations of the present trial

The study does not include dose-escalation or de-escalation arm—precluding exploration of dose–response relationships. Furthermore, all participating sites are located in Xi’an, limiting generalizability of the results. Larger, multi-centre studies with diverse populations are warranted. This prospective, randomised, single-blind, controlled trial will evaluate the efficacy and safety of Rǔ-Mò Zhèn-Tòng-Yǐn combined with standard Western therapy versus standard therapy alone in patients with OPP. The primary end-points are improvement in BMD and pain relief. Secondary end-points include changes in bone-turnover markers, inflammatory cytokines and TCM syndrome scores. The findings are expected to provide robust evidence for the integrative management of osteoporotic pain.

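### The article names the primary endpoint in three ways that cannot all be true, and only VAS pain has a sample-size basis

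*Protocol article*

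**What the plan says.** Three sections of the Protocol article define the primary endpoint.

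- **Abstract, Methods:** "Primary outcome was pain scores; secondary outcomes included bone mineral density (BMD), bone-turnover markers, inflammatory cytokines". Pain is the only primary outcome.
- **Outcomes:** "Primary endpoints: Pain score: Visual Analogue Scale (VAS); Mechanism indicators: 1.Bone-mineral density (BMD", followed by "2.Bone-turnover markers: β-CTX and PINP; 3.Inflammatory cytokines: TNF-α and IL-1". The separate secondary list reads "Secondary endpoints:1.Blood-stasis syndrome score; 2.Hematological indices: serum MCV, RDW-CV, MPV and PDW" and contains none of the five mechanism indicators.
- **Limitations of the present trial:** "The primary end-points are improvement in BMD and pain relief". Turnover markers and cytokines are secondary here.

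The Sample size section uses VAS improvement only. It assumes 2.45 versus 2.07 with SD 0.53, two-sided α of 0.05 and power 0.95, and arrives at 51 per arm, or 57 after 10% attrition. The Statistical analysis section names a generic between-group test (t-test or Mann–Whitney U) and adds: "All tests will be two-tailed, with a significance level set at P < 0.05".

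**The concern.** The primary endpoint decides what counts as a positive trial. BMD is secondary in the Abstract and primary in the Limitations section. The turnover markers and cytokines are secondary in both of those places, yet sit under the primary heading in Outcomes. A report could therefore cite one section or another to support a primary claim on pain, on BMD, or on a laboratory marker. The documents give an effect size for VAS only, so any other endpoint called primary has no stated power. Whether the ambiguity costs type I error or power depends on whether one success is enough or all are needed, and the article does not say.

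**Working it through.** **1. The three definitions side by side**

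| Variable | Abstract | Outcomes | Limitations |
|---|---|---|---|
| VAS pain | primary | primary | primary |
| BMD | secondary | under primary heading | primary |
| β-CTX, PINP | secondary | under primary heading | secondary |
| TNF-α, IL-1 | secondary | under primary heading | secondary |

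The number of primary variables is 1 in the Abstract, 2 in the Limitations section, and 1 + 5 = 6 in Outcomes on its most natural reading.

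**2. The plan's own figure**

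Difference = 2.45 − 2.07 = 0.38; SD = 0.53.

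n per arm = 2 × (1.960 + 1.645)² × 0.53² / 0.38² = 2 × 12.99 × 0.2809 / 0.1444 ≈ 50.6, rounded up to 51.

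With 10% attrition, 51 / 0.90 = 56.7, rounded up to 57 per arm, 114 in total. The stated figures reproduce. An exact noncentral-t calculation gives 52 per arm, with power 0.948 at 51; the difference is immaterial. The calculation is for one VAS test at two-sided 0.05 and nothing else.

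**3. If any one primary endpoint at P < 0.05 counted as success**

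Chance of at least one false positive among k independent tests = 1 − 0.95^k.

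- k = 1: 0.05
- k = 2: 1 − 0.9025 = 0.0975 (9.8%)
- k = 6: 1 − 0.7351 = 0.2649 (26.5%)

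The documents give no correlations. A simulation of equally correlated normal test statistics (1,000,000 draws each), with assumed values, gives:

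| Assumed correlation | 2 endpoints | 6 endpoints |
|---|---|---|
| 0.3 | 9.5% | 24.1% |
| 0.5 | 9.0% | 20.8% |
| 0.8 | 7.8% | 13.8% |

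**4. If all primary endpoints had to succeed**

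Alpha does not inflate. Joint power, if each endpoint had 0.95 power and they were independent, would be 0.95² = 0.9025 for two and 0.95⁶ = 0.735 for six. The 0.95 for endpoints other than VAS is itself only an assumption.

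**5. Dates**

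The Trial status section says that "actual enrollment commenced on 12 September 2025". The Abstract dates registration to 2026-01-08. The interval is 18 + 31 + 30 + 31 + 8 = 118 days.

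**The case against.** Four objections deserve weight.

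- **The mechanism indicators may be a separate category.** They follow a semicolon and carry their own label and numbering. That reading is possible and would remove the six-variable version. Against it, the heading is plural and the secondary list contains none of the five. Even if it is accepted, the Abstract and the Limitations section still disagree on BMD.
- **An unseen analysis plan may hold the multiplicity rule.** This stands. A reader might infer that the trial has no fixed test and no error control, and the documents do not support that. The Statistical analysis section names a test and a 0.05 level, and the Abstract's version, with one visit fixed, would hold alpha at 5%. A missing hierarchy or adjustment is therefore not the finding. No analysis plan, however, can make three conflicting published definitions all true.
- **The error rates are conditional.** This also stands. A reader might take 26.5% as the trial's type I error. It applies only under an any-endpoint rule that no section states, with six independent primary endpoints.
- **The registry may already be right.** Its endpoint is not shown in the article, so it cannot be called wrong. The dates show only that it is not a pre-enrolment record.

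The VAS-only sample size suggests that pain was the intended primary endpoint. That supports the fix but does not remove the contradiction.

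**Conclusion.** The contradiction is certain and stands in current text: one, two, or most naturally six primary variables, depending on the section. What is not fixed is the endpoint and the rule for success; a generic test and level are stated.

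The size depends on that rule. If any one success sufficed, the family-wise error would be 9.8% (two) or 26.5% (six) under independence, falling to about 8% and 14% at an assumed correlation of 0.8. If all were required, the stated 95% power would not describe the trial. With VAS as the sole primary endpoint at one visit, alpha stays at 0.05 and the calculation of 51, inflated to 57, per arm stands. This must be fixed, because it determines what the trial may claim.

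**What to change.** Before unblinding, name VAS change from baseline at one pre-specified visit as the sole primary endpoint, in the same words in the Abstract, Outcomes and Limitations sections. VAS is the only endpoint that the sample size supports.

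- **Visit.** The article fixes none, so the investigators should specify it; end of treatment is the natural choice. They should also reconcile Table 1 (days 30, 60 and 90) with the four-weekly follow-up in the Study design and Sample size sections, which would put visits at days 28, 56 and 84.
- **Other variables.** List BMD, β-CTX, PINP, TNF-α and IL-1 as secondary or exploratory outcomes that cannot support a primary claim.
- **Approvals.** Check the choice against the ethics-approved version and submit an amendment if it differs. Align the registry entry if needed, and state that registration came 118 days after enrolment began.

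The cost is wording changes and possibly an ethics amendment, with no extra patients or data. A BMD or marker result alone would no longer count as primary success. There is still time: recruitment runs to 31 December 2026, and the allocation code stays concealed until after database lock.

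### The safety endpoints omit the adverse events that Table 1 logs, and the unrestricted LOCF rule can score early withdrawals for harm as unchanged on five safety measures

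*Protocol article*

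**What the plan says.** The Outcomes section lists the safety endpoints in one sentence: "Safety endpoints:Height, blood pressure, 12-lead ECG, routine hematology, liver and renal function tests, and coagulation profile". Counting liver and renal function separately, that is seven items, all of them examinations or laboratory tests.

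Table 1 (printed in the Introduction) covers more. Under its safety observations it has an "Adverse-event log" marked at days 30, 60 and 90. Its closeout rows record withdrawals and drop-outs, a compliance and safety evaluation form, and abnormal findings.

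The withdrawal/discontinuation criteria include "Occurrence of serious side-effects, adverse reactions, or allergic reactions". No assessment at the time of withdrawal is mentioned.

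The Statistical analysis section has a single missing-data rule: "Missing values will be imputed by last-observation-carried-forward (LOCF) method". It names no class of variable to which the rule does or does not apply.

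The closing summary, under Limitations of the present trial, says that the trial "will evaluate the efficacy and safety of" the decoction added to standard therapy.

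**The concern.** Two statements in the article work against its safety aim.

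First, the endpoint list and the visit schedule disagree. Adverse events are collected, but they are not among the endpoints on which the arms are to be compared. An analysis that follows the Outcomes section would report laboratory and examination results and need not report event incidence.

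Secondly, LOCF assumes that a participant who leaves would have stayed at the last recorded value. When the reason for leaving is an adverse reaction, and the last recorded value was taken before treatment began, the imputed result says that nothing happened. Missingness is then related to harm, and the imputation pushes the comparison towards no difference. At stake is the credibility of a finding of no difference on blood pressure, ECG, haematology or coagulation.

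**Working it through.** **1. Which measures are exposed.** From the safety rows of Table 1:

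| Safety endpoint | Screening | Day 30 | Day 60 | Day 90 |
|---|---|---|---|---|
| Height | × | | | × |
| Blood pressure | × | | | × |
| ECG | × | | | × |
| Haematology | × | | | × |
| Coagulation | × | | | × |
| Liver function | × | × | × | × |
| Renal function | × | × | × | × |

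Five of the seven (5/7 = 71%) have no scheduled value between screening and day 90.

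**2. What LOCF does to an early withdrawal.** Let Y0 be the screening value and suppose that no unscheduled test is done.
- For the five measures, leaving at any time before day 90 gives an imputed day-90 value of Y0, so the change is Y0 − Y0 = 0.
- For liver and renal function, leaving before day 30 also gives 0. After that, the day-30 or day-60 value is carried, so a change of zero is not forced.
- "Blood-cell indices" appear in Table 1 as an efficacy item at all four time points. Part of the blood count is therefore seen more often than the haematology row suggests.

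If LOCF were read as carrying only post-baseline values, the participant would have nothing to carry on the five measures and would drop out of the comparison. The harm would be missing from it under that reading too.

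**3. Group size for the illustration.** The Sample size section gives a difference of 2.45 − 2.07 = 0.38, SD 0.53, two-sided α = 0.05 and power 0.95. The normal approximation gives n = 2 × (1.960 + 1.645)² × (0.53/0.38)² = 2 × 12.99 × 1.945 ≈ 50.6, so 51 per arm. Then 51/0.90 = 56.7, so 57 per arm. The stated figures reproduce. The planned attrition allows for 57 − 51 = 6 losses per arm, for any reason.

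**4. Illustration with assumed counts.** The article gives no adverse-reaction rate, so the counts below are assumptions. Take x of 57 participants on the decoction and 0 of 57 controls with an abnormal ECG, coagulation or haematology finding, all with normal screening values. With no control events and equal arms, the two-sided Fisher p-value is 2 × C(57, x)/C(114, x).

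| True count | Withdrawn early, screening value carried | Count seen | p before | p after |
|---|---|---|---|---|
| 6/57 (10.5%) | 3 | 3/57 (5.3%) | 0.027 | 0.24 |
| 6/57 (10.5%) | 6 | 0/57 | 0.027 | 1.0 |
| 3/57 (5.3%) | 3 | 0/57 | 0.24 | 1.0 |
| 9/57 (15.8%) | 6 | 3/57 (5.3%) | 0.003 | 0.24 |

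The loss comes from the carried-forward screening values. In every row the log would still hold the events.

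**The case against.** The strongest reply is that the events are not lost. The log runs through treatment, closeout forms record withdrawals and abnormal findings, and an independent committee reviews safety every 6 months. The categorical tests already named in the Statistical analysis section could compare event incidence by arm. This stands. A reader might infer that a harm signal could vanish from the trial, that people with reactions are recorded as having none, or that safety cannot be evaluated at all. The documents support none of these. LOCF cannot alter a logged event, and the effect is confined to the comparison of the scheduled measures.

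A second reply is that the forced zero is not a stated rule. The article does not say that a screening value is carried forward, nor that no test is done when a reaction occurs. This stands in part: the zero depends on both conditions. But the sentence excludes neither, and the alternative reading removes the same participants from the comparison.

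A third reply is that detailed safety analysis may sit in a full protocol or SAP that is not shown. That is fair for populations and tabulations, and their absence is not criticised here. The point rests on what the article does state: an endpoint list that disagrees with its own schedule, and an imputation rule without limits.

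Finally, the counts are assumed. The example of 6/57 versus 0/57 does not estimate this trial's adverse-reaction rate, and its p of 0.027 on its own measures no loss. Only the before-and-after contrast does.

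**Conclusion.** The point holds in a limited form. The safety endpoint list omits events that the trial already logs. Applied as written, LOCF biases the between-arm comparison towards no harm on height, blood pressure, ECG, haematology and coagulation. For liver and renal function a zero change is forced only for withdrawals before day 30.

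The size depends on how many participants withdraw for reactions before day 90 without an unscheduled test, which the article does not allow one to estimate. Under the assumed counts, three early withdrawals out of six affected move p from 0.027 to 0.24, and six out of six remove the difference on those measures. The sample size is not affected.

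This should be corrected, since it concerns stated rules and not merely missing detail. It does not invalidate the trial's safety data.

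**What to change.** In Outcomes, add to the safety endpoints the incidence by arm of any adverse event, of serious adverse events, and of adverse events leading to withdrawal. Take these from the existing log, in all participants who started treatment.

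In Statistical analysis, state that LOCF does not apply to safety variables. Analyse observed safety values, including any obtained at withdrawal, and report by arm the number missing at each scheduled assessment with the reasons.

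The cost is wording in two sections and one extra table, from data already scheduled for collection. By the article's own dates, recruitment runs to 31 December 2026 and the group code stays sealed until after database lock, so the change can be made before unblinding.
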